### Adherence

To follow the participants and ensure their adherence to diet and receive supplements, participants will be contacted by telephone once a week. At every phone call, we will make sure if the cases are still in the study and they do not have exclusion criteria. Also, a 24-h recall is taken from patients on each phone call to ensure adherence to the diet. At the end of the sixth and twelfth weeks, the participants are followed up and evaluated in person. Individuals are asked to return unused supplements; if less than 90% of supplements are taken, the person will be excluded from the study. Data from patients who are more than 90% consistent with the intervention will be analyzed.

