### Inclusion and exclusion criteria

For this study, 50 patients with weight regain and food addiction and with the following inclusion criteria will be included in the study: aged 18–50 years; BMI ≥ 25 kg/m2; willingness to participate in the study; not having diseases such as cancer, thyroid, renal or liver (except fatty liver); non-pregnant or lactating or menopause or professional athlete; not use of any antibiotics in the last three weeks and any protein or probiotic supplement in the last month.

Patients will be excluded if: taking any antibiotics during the study; using probiotic products (probiotic supplements, yogurt, cheese, cakes, biscuits, and probiotic pasta) or protein supplements during the study; using weight-loss or appetite-suppressing medications; pregnancy; consuming less than 90% of the supplements prescribed during the study Also, we will exclude participants who refuse to continue the study.

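### The only stated analysis set is selected on adherence and other post-randomisation events, so the arms compared are not the randomised arms

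*Protocol article*

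**What the plan says.** The Adherence section sets the capsule rule, "if less than 90% of supplements are taken, the person will be excluded from the study", and then defines whose data count: "Data from patients who are more than 90% consistent with the intervention will be analyzed". It also says that staff check at each weekly telephone call that participants are still in the study and do not meet an exclusion criterion.

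The section on inclusion and exclusion criteria repeats the capsule rule ("consuming less than 90% of the supplements prescribed during the study") and lists other grounds for removal. They include "taking any antibiotics during the study", probiotic or protein products during the study, "using weight-loss or appetite-suppressing medications" and pregnancy. The list ends with "we will exclude participants who refuse to continue the study".

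The Statistical analysis section names the tests (paired and unpaired t-tests, their non-parametric counterparts, repeated-measures ANOVA, covariance analysis, chi-square and regression). It mentions no analysis of all randomised participants. The Sample size section allows for a 20% drop, from 20 to 25 per arm.

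**The concern.** Capsule intake over 12 weeks, antibiotic use and refusal to continue are known only after allocation. A set defined by them is not protected by randomisation. The danger is greatest where the event is linked to the outcome. Weight is the variable used for sizing and one of the primary outcomes. A patient who is not losing weight has more reason to start a weight-loss drug, stop the capsules or leave. Tolerability could also differ between active and placebo capsules, although the documents give no data on this.

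A between-arm difference in weight or food addiction score could then partly reflect who was removed and not what the probiotic did. The rule also governs data collection. If those removed are not measured again, an analysis of all randomised participants cannot be recovered later.

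This is not a detail left to an unseen analysis plan. The protocol article itself states the restricted set.

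**Working it through.** **Inputs from the protocol article.** Sample size section: SDs 2.8 and 2.9, difference 2.5, two-sided alpha 0.05, power 80%, 20 per arm raised to 25. Intervention section: 2 capsules daily for 12 weeks.

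**1. The plan's own sample size.** (2.8² + 2.9²)/2 = 8.125, so the figure labelled Sp is the pooled variance, and SD = √8.125 = 2.85. Then n = 2 × 8.125 × (1.960 + 0.842)² / 2.5² = 20.4, against 20 stated, and 20/0.8 = 25. The plan's figures reproduce to within rounding. The 20% allowance protects the number analysed, not the comparability of the arms.

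**2. How strict the rule is.** 2 × 84 = 168 capsules, and 0.9 × 168 = 151.2. A participant must take at least 152, so at most 16 may be missed over 12 weeks. The text removes those under 90% and analyses those over 90%. Exactly 90% is undefined but cannot occur with 168 whole capsules.

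**3. Bias with no true effect (assumed model).** Let removal fall on the poorer responders, with correlation r between staying in and weight loss. If a proportion p is removed from an arm, the mean of those retained shifts by r × SD × φ(z_p)/(1 − p). The bias is the difference of these shifts between arms. The factor φ(z_p)/(1 − p) is 0.195 at p = 10%, 0.350 at 20% and 0.497 at 30%. The example for 20% v 0% and r = 0.5 is 0.5 × 2.85 × 0.350 = 0.50 kg.

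Type I error is taken from the noncentral t with the remaining numbers. For 20 v 25, SE = 2.85 × √(1/20 + 1/25) = 0.855 kg.

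| Removed (arm A v arm B) | Analysed | Bias at r = 0.3, 0.5, 0.7 (kg) | Type I error |
|---|---|---|---|
| 20% v 0% | 20 v 25 | 0.30, 0.50, 0.70 | 6.4%, 8.8%, 12.6% |
| 30% v 10% | 17 v 22 | 0.26, 0.43, 0.60 | 5.9%, 7.4%, 9.8% |
| 25% v 15% | 19 v 21 | 0.13, 0.21, 0.30 | 5.2%, 5.6%, 6.2% |
| 20% v 20%, same r | 20 v 20 | 0 | 5% |

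**4. A second, simpler model.** Suppose those removed do g kg worse than those retained. The bias is then (proportion removed in A × g in A) − (proportion removed in B × g in B).
- 30% v 10%, g = 2 kg in both arms: 0.6 − 0.2 = 0.4 kg.
- 30% v 10%, g = 4 kg in both arms: 1.2 − 0.4 = 0.8 kg.
- 20% v 20%, g = 2 kg in one arm and 0 in the other: 0.4 − 0 = 0.4 kg. Equal removal rates alone are therefore no safeguard.

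With 20 per arm (SE 0.90 kg, normal approximation), shifts of 0.4 and 0.8 kg give type I errors of 7.3% and 14.4%.

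**5. Power if all 25 per arm are analysed (noncentral t, SD 2.85).** With the full 2.5 kg effect, power is 86.0%. If 20% of the active arm gain nothing, the effect is 0.8 × 2.5 = 2.0 kg and power is 68.1%. The planned 20 per arm at 2.5 kg gives 77.1% by the same method.

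**The case against.** Four points can fairly be made for the plan.

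- **Scope.** The sentence on the analysed set refers only to consistency with the intervention. That data are also discarded for the other listed events is inferred from their being exclusions, and the weight-loss drug item, unlike the antibiotic item, is not tied to the study period. The inference is nevertheless sound, because the Adherence section re-checks exclusion criteria at every weekly call. The capsule rule alone would be enough for the concern.
- **Blinding.** The trial is described as triple-blind, and the capsules are alike in shape, size and colour. This makes removal driven by poor weight loss more likely to act alike in both arms when there is no true effect. It lowers the risk. It does not rule out differences due to tolerability or, if the probiotic works, due to response.
- **Size.** The plan assumes the same 20% drop in each group. Equal removal of similar patients gives no bias, and 25% v 15% gives at most 0.30 kg at r = 0.7. Even 0.70 kg is 28% of the planned effect (0.70/2.5). This stands: the size and direction of the bias are unknown, and with few removals it would be small.
- **Missing data.** Some who refuse to continue will have no week-12 weight, so analysing everyone as allocated still needs a missing-data method. That is true, and the method can be set in the analysis plan. It is no reason to discard participants who can be measured.

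These points limit how large the bias may be. None supplies an analysis that keeps the randomised comparison.

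**Conclusion.** The concern holds. The protocol article commits to analysing a set selected by events after randomisation and states no analysis of all randomised participants. The estimate is therefore open to selection bias on weight and on every other between-arm outcome.

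Under the unequal-removal scenarios in the table, the bias on weight runs from 0.13 to 0.70 kg and the type I error from about 5% to 13%. It is zero if removal rates and the kind of patient removed are the same in both arms. These figures rest on assumed removal rates and correlations and on treating 2.85 kg as the SD of weight change, which the Sample size section does not say outright. The presence of the defect does not depend on them. It must be fixed, because a causal reading of the result would otherwise need an assumption about the removed participants that the trial could not check.

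**What to change.** - State that the primary analysis includes all randomised participants in their allocated arm, whatever their capsule count or use of antibiotics or other products.
- In the Adherence section, replace removal from the study for low capsule intake with recording a protocol deviation, and keep inviting these participants to the week-6 and week-12 assessments. The change concerns measurement and analysis only. It does not alter any rule on who continues or stops capsules.
- Keep the set with at least 90% intake as a labelled sensitivity analysis.
- Set the handling of missing week-12 data in the analysis plan.

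The cost is a wording amendment and the effort of bringing those who stop capsules to two visits that are already scheduled. The drawback is possible dilution of the effect, with power of about 68% if it falls to 2.0 kg and 86% if it does not fall. The protocol article describes the trial as still enrolling, so early amendment matters: participants already removed may have no week-12 measurement.

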### Study outcomes

The primary outcomes of this clinical trial are the changes in anthropometric indices (including weight, hip circumference, waist-to-hip ratio, fat mass, muscle mass) and food addiction score. Secondary outcomes are changes in eating behavior and serum levels of leptin, serotonin, and oxytocin.

If the patient has inclusion criteria, a consent form and personal information sheet will be completed for them.

Food addiction will be diagnosed using a Modified Yale Food Addiction Scale Version 2.0 questionnaire. In this questionnaire, 12 criteria are examined. Both the symptom count score and the clinical significance criterion are used. For the "diagnosis" scoring option, a participant can meet for mild, moderate, or severe food addiction. At the beginning of the study, in the middle of the study (sixth week), and at the end of the study (twelfth week), anthropometric measurements, body composition, and calculation of body mass index will be done for each person. A digital scale will measure weight with an accuracy of 0.1 kg, with minimal clothing and no shoes. Height, waist, and hip circumference will be measured with an inelastic meter with an accuracy of 0.5 cm. Waist circumference will be measured at a distance between the lowest rib and iliac bone and hip circumference at the highest hip protrusion. Body mass index and waist-to-hip ratio are obtained by calculation. Body fat mass and muscle mass will be measured by bioelectrical impedance analysis (BIA). The participants' physical activity level is assessed using the standard questionnaire of activities (metabolic equivalents task) (MET) at the start, the sixth week, and the end of the study. Eating behavior is assessed using the Three-Factor Eating Questionnaire (TFEQ-R18) at the beginning, sixth week, and end of the study. Three 24-h food recall (2 regular days of the week and one day off) will be taken from participants at the beginning, the sixth week, and end of the study, also, a 24-h recall once a week, with telephone calls with patients. To measure blood biochemical parameters, at the beginning and end of the study, after 12–14 h of night fasting, five cc of venous blood samples will be taken from the participants. Blood samples taken in tubes containing sodium citrate anticoagulants will be collected and centrifuged in the laboratory of the Shahid Beheshti Nutrition Faculty. Serums will be stored at -80 °C until the tests are performed. Serum levels of leptin, serotonin (LDN ELISA Kit, Germany), and oxytocin (Crystal Day ELISA Kit, Shanghai) will be measured by the ELISA method with the human kit with the intra-assay and inter-assay CV of < 10.8% (serotonin), < 12% (leptin), and < 6.8% (oxytocin) kits in the laboratory of the Nutrition Institute of Shahid Beheshti University of Medical Sciences.

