### Sample size

The number of samples required for this study was calculated based on weight as a main dependent variable. The results of a previous study were used to calculate the sample size [47]. Sample size was calculated with α = 0.05 and power of 80% (1-β = 0.8). the sample size in each group was determined to be 20 patients; assuming a drop of 20%, 25 patients will be admitted to each group.

$$\begin{array}{c}\mathrm S1=2.8\\\mathrm S2\;=2.9\\\mathrm{Sp}\;=\;8.125\\\mathrm\mu1-\mathrm\mu2=2.5\\\end{array}$$

$$\begin{array}{c}\mathrm n=\frac{2\mathrm{Sp}^2\left({\mathrm Z}_{1-{\displaystyle\frac{\mathrm a}2}}+{\mathrm Z}_{1-\mathrm\beta}\;\right)^2}{\left(\mathrm\mu1-\mathrm\mu2\right)^2}\end{array}$$

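### Six primary outcomes in an open-ended list, but a trial sized for weight alone at a single 0.05 level

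*Protocol article*

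**What the plan says.** The Study outcomes section states: "The primary outcomes of this clinical trial are the changes in anthropometric indices (including weight, hip circumference, waist-to-hip ratio, fat mass, muscle mass"), and adds the food addiction score. That is six named outcomes. The five anthropometric ones are introduced by *including*. The same section has BMI and waist circumference measured or calculated as well ("Body mass index and waist-to-hip ratio are obtained by calculation"), but lists neither as primary or secondary by name.

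The Sample size section rests on one variable: "The number of samples required for this study was calculated based on weight as a main dependent variable". It gives one error rate and one power: "Sample size was calculated with α = 0.05 and power of 80% (1-β = 0.8"). The printed formula uses the two-sided normal quantile. The result is: "the sample size in each group was determined to be 20 patients; assuming a drop of 20%, 25 patients will be admitted to each group".

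The Statistical analysis section describes a between-group t-test or Mann–Whitney test for quantitative variables, applied variable by variable. It does not rank the primary outcomes or set a separate significance level for any of them.

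**The concern.** A primary outcome list tells the reader which result decides whether the trial succeeded. Here the outcome section gives that status to six variables, while the sample size gives only one of them a designed power and an error rate.

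Followed as written, a significant change in hip circumference or muscle mass could be reported as a met primary outcome even if weight, the only variable with a power calculation, showed no difference. The 5% error rate assumed in the sample size would then not describe the claim being made. The open wording adds to this, because a reader cannot tell from the text whether the family is exactly six.

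**Working it through.** **Inputs from the Sample size section.** SDs 2.8 and 2.9; difference 2.5; two-sided alpha 0.05; power 80%; 20 per group, 25 after 20% dropout. From Study outcomes: six named primaries. The document gives no correlations between them, so a common correlation from 0 to 0.9 is assumed.

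**1. Reproduce the plan's figure.** Pooled variance = (2.8² + 2.9²)/2 = 8.125, so SD = 2.850. The value printed as Sp is this variance, and it is used as a variance here.

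n = 2 × 8.125 × (1.960 + 0.842)² / 2.5² = 20.4 per group. The plan states 20, which agrees to within rounding. Dropout: 20/0.8 = 25. The calculation therefore belongs to one test of weight at a full two-sided 0.05.

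**2. Family-wise error for six tests at 0.05, no true effect on any, any one counting as success.**

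Independent: 1 − 0.95⁶ = 0.265.

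For equally correlated normal test statistics, the probability that at least one of six exceeds 1.960 in absolute value is:

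| Assumed common correlation | Family-wise error |
|---|---|
| 0 | 26.5% |
| 0.3 | 24.1% |
| 0.5 | 20.7% |
| 0.7 | 16.4% |
| 0.8 | 13.9% |
| 0.9 | 10.8% |

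A less uniform pattern falls in the same range. With the five anthropometric indices correlated at 0.7 and the food addiction score uncorrelated with them, the figure is 19.1%.

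**3. Could the existing sample carry a split alpha?** Bonferroni over six gives 0.05/6 = 0.00833 per test.

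Noncentrality for weight at 20 per group = 2.5 / (2.850 × √(2/20)) = 2.77.

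The two-sided critical t on 38 degrees of freedom at 0.00833 is 2.78, which gives power of about 50% from the noncentral t distribution. The normal approximation, with critical value 2.638, gives 55%.

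Restoring 80% would take 2 × 8.125 × (2.638 + 0.842)² / 2.5² = 31.5, so 32 per group, or 32/0.8 = 40 after dropout, against 25 planned.

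**The case against.** Several points on the other side are fair.

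- **The 0.05 per test is inferred.** It appears only in the sample size calculation. An analysis plan that is not shown may hold an order of testing or an adjustment, so the lack of a multiplicity rule in the article is not the finding. What remains is what the article itself fixes: six primaries against a size for one. A later split of alpha would cost the power stated for weight, and a later choice of one primary would depart from the outcome section, so the mismatch does not go away.
- **The inflation depends on a success rule.** A reader might infer that the trial's false positive rate simply is 16–26%. The document does not support that: it says neither that any one result suffices nor that all six are needed. If all six were required there would be no inflation. The lower end also depends on where the assumed correlation stops.
- **Adding BMI and waist circumference.** A reader might count eight tests and quote 1 − 0.95⁸ = 34%. That figure should not be used. In adults of fixed height, BMI change is weight change rescaled, and waist circumference follows from hip circumference and waist-to-hip ratio, so eight independent tests are impossible. That these two could be added later is only a possible reading of *including*, which may simply introduce the list.
- **Contradiction is too strong a word.** Weight is "calculated based on weight as a main dependent variable" in one section and is among the primaries in the other. Sizing on one of several primaries is a mismatch; the statements do not exclude each other.
- **Food addiction is central to the trial.** It is an entry condition and part of the stated aim. A co-primary or split-alpha scheme would also control the error, but step 3 shows what a six-way split costs.

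**Conclusion.** The point stands in conditional form. The article names six primary outcomes in a list that is not closed, and sizes the trial on weight alone at a single two-sided 0.05. If each is tested at 0.05 and any one significant result counts as success, the family-wise error under the global null is about 11–26% for assumed common correlations from 0.9 down to 0 (16% at 0.7). That is at least twice the nominal 5% throughout the range. The count of six and the sizing on weight are certain from the text; the percentage rests on the per-test level, the success rule and the correlations, none of which the document states. The present sample cannot absorb a Bonferroni split over six without power for weight falling to about 50%.

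**What to change.** In Study outcomes, name change in body weight at week 12 as the single primary outcome, in line with the Sample size section. Replace the open wording with a closed list, and make hip circumference, waist-to-hip ratio, fat mass, muscle mass and food addiction score secondary. If the food addiction score is to remain confirmatory, test it second, at 0.05, and only if weight is significant; this fixed order holds the family-wise error at 5% without reducing alpha for weight.

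The change adds no patients, visits or measurements. Its cost is that five outcomes lose the primary label, and the food addiction score gets a confirmatory test only if weight succeeds. The article describes the trial as still enrolling, so this is an amendment during recruitment. It needs agreement under the Modification of study section, with ethics committee approval if it is judged to be a change of the kind listed there. The registry entry, which is not at hand, should be updated to match. The amendment should be dated and completed before unblinding.

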### Statistical analysis

In this study, data analysis will be performed by using SPSS version 21.0 (SPSS Inc, Chicago, Illinois) software. A paired t-test will be used to compare the mean of quantitative variables with normal distribution in each group between the beginning and the end of the study. The t-test will be used to compare the mean between the two groups at the beginning and end of the study. In the case of quantitative variables with non-normal distribution, Wilcoxon and Mann–Whitney tests are used, respectively. A repeated ANOVA test will be used for the variables measured three times during the study. Covariance analysis will be used to eliminate the effect of quantitative confounding factors. Quantitative confounding factors are physical activity and baseline values of the biochemical markers. A Chi-square test will be used to compare the qualitative variables between the two groups, and regression analysis will be used to eliminate the effect of qualitative confounding.

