
### Objectives and hypothesis

This study aims to investigate the effect of probiotic supplementation with a weight-reducing diet and psychotherapy intervention on anthropometric measures, body composition, eating behavior, and related hormone levels (leptin, serotonin, oxytocin) in patients with food addiction and weight regain after bariatric surgery.

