### Intervention

For all participants in this study, the standard hypocaloric diet (-300 to -500 kcal from total energy requirement) is calculated based on basal metabolism (use of indirect calorimeter) and level of physical activity. The diet in each group will consist of 45% carbohydrates, 25% protein, and 30% fat. For all participants in the study, ten one-hour online individual sessions, once a week, will be performed cognitive behavioral therapy (CBT) intervention by a psychologist. This study will randomly divide participants into groups receiving a probiotic supplement or placebo. All participants are asked to take 2 capsules daily (after breakfast and after lunch) for 12 weeks. Capsules are given to participants at the beginning of the study and in the sixth week of the study, and they are asked to return the unused capsules. To follow the participants and ensure their adherence to diet and receive supplements, participants will be contacted by telephone once a week. Also, the participants will be followed up and evaluated in person at the end of the sixth and twelfth weeks. Because multi-strain probiotics are more effective than single-strain probiotics [49, 50], multi-strain probiotics will be used in this study. Each probiotic capsule contains Lactobacillus acidophilus (1.8 × 109 CFU / capsule), Bifidobacterium bifidum (1.8 × 109 CFU / capsule), Bifidobacterium lactis (1.8 × 109 CFU / capsule), Bifidobacterium longul / C, 1.8 (1 × 109 CFU / capsule), Lactobacillus reuteri (1 × 109 CFU / capsule), magnesium stearate and maltodextrin. The placebo capsule contains 300 mg of starch. The capsules are similar in shape, size, and color and are provided by Takgen Zist Company in Iran.

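### Within-arm before/after tests stand unranked beside the between-arm tests, although diet and CBT go to both arms and within-arm change cannot show a probiotic effect

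*Protocol article*

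**What the plan says.** The Statistical analysis section of the protocol article opens with a within-arm test, baseline against week 12: "A paired t-test will be used to compare the mean of quantitative variables with normal distribution in each group". The between-arm test follows: "The t-test will be used to compare the mean between the two groups at the beginning and end of the study". Non-normal variables get the rank-based counterparts of each: "In the case of quantitative variables with non-normal distribution, Wilcoxon and Mann–Whitney tests are used, respectively". Two further analyses are named. One is "A repeated ANOVA test will be used for the variables measured three times during the study", without saying which term (time, group or their interaction) is to be tested. The other is a covariance analysis, for which "Quantitative confounding factors are physical activity and baseline values of the biochemical markers".

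The section does not rank these analyses or label any of them descriptive.

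Four other sections bear on this:
- **Intervention:** the diet and the ten weekly CBT sessions go to everyone ("For all participants in this study, the standard hypocaloric diet (-300 to -500 kcal from total energy requirement"). Only the capsule, probiotic or placebo, is randomised.
- **Study population:** entry requires an mYFAS 2.0 diagnosis of food addiction.
- **Study outcomes:** the primary outcomes are changes in anthropometric indices, including weight, and in the food addiction score.
- **Sample size:** the calculation uses a two-group formula with a between-group difference of 2.5.

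**The concern.** A paired test within one arm asks whether that arm changed. In this trial an arm can change for reasons unrelated to the capsule: the energy deficit, the CBT, the passage of time and, for the food addiction score, regression to the mean after selection on a high score. These act equally on both arms, so only the probiotic-minus-placebo contrast removes them.

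Two misreadings become possible when within-arm p-values sit beside between-arm p-values with no order among them. The first takes a significant fall in the probiotic arm as evidence for the probiotic. The second takes significance in the probiotic arm, with none in the placebo arm, as evidence of a difference between arms. Neither inference controls the error rate at 5%. What is at stake is a false claim for the probiotic on weight or food addiction score.

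**Working it through.** **Inputs from the protocol article (Sample size).** SDs 2.8 and 2.9; between-group difference 2.5; two-sided α 0.05; power 80%; 20 evaluable per arm, 25 enrolled.

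**The plan's own figure.** The pooled variance is (2.8² + 2.9²)/2 = (7.84 + 8.41)/2 = 8.125, so the pooled SD is √8.125 = 2.85. The printed Sp of 8.125 is thus a variance; that labelling is a separate matter and does not affect this point. Then n = 2 × 8.125 × (1.960 + 0.842)² / 2.5² = 20.4, consistent with the stated 20. Allowing for 20% dropout, 20/0.8 = 25. The sample size therefore already rests on the between-arm contrast.

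**Assumptions.** The article does not say whether 2.8 and 2.9 are SDs of weight or of weight change; they are taken here as SDs of change, in kg. It gives no expected within-arm weight loss, so a range is used. The capsule is taken as inert, so both arms have the same true mean loss d.

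**Chance of a significant paired t-test in one arm.** The noncentrality is d/(SD/√n), with SD/√n = 2.85/√20 = 0.637, 19 degrees of freedom and a critical t of 2.093. An observed mean loss of 2.093 × 0.637 = 1.33 kg is enough for significance.

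| Mean loss d (kg) | Noncentrality | P(significant in an arm) = p | P(probiotic arm only) = p(1−p) |
|---|---|---|---|
| 0.5 | 0.78 | 12% | 10% |
| 1.0 | 1.57 | 32% | 22% |
| 1.5 | 2.35 | 61% | 24% |
| 2.0 | 3.14 | 85% | 13% |
| 2.5 | 3.92 | 96% | 4% |
| 3.3 | 5.18 | over 99% | under 1% |

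The last row corresponds to full adherence to the smaller deficit: 300 × 84/7,700 = 3.3 kg, assuming 7,700 kcal per kg. The larger deficit gives 500 × 84/7,700 = 5.5 kg.

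With an SD of change of 5 kg instead, p is 14% at 1 kg, 57% at 2.5 kg and 79% at 3.27 kg.

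**Significant in the probiotic arm only.** The arms are independent, so this has probability p(1−p). It peaks at 0.5 × 0.5 = 25%. A two-sided 5% between-arm test errs in that direction 2.5% of the time.

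**Between-arm test under the same conditions.** In 100,000 simulated trials with a 2.5 kg mean loss in both arms, SD 2.85 and 20 per arm, the paired test was significant in 96% of arms of either kind. The two-sample t-test on change was significant in 5.0% of trials.

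**Regression to the mean in the food addiction score.** Assume a normally distributed score, entry above a cut-off matching the 14–58% prevalence quoted in the Background, and a retest correlation of 0.5 to 0.9. Regression to the mean alone then makes the paired test significant in 10% to 97% of arms of 20. The size is uncertain, but the direction favours apparent improvement in both arms.

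**Leptin, serotonin, oxytocin.** The article gives no expected change for these, so no probability can be attached.

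**The case against.** The strongest reply is that the trial is already built around the between-arm contrast. It randomises against placebo, sizes on a between-group difference, and names a between-group t-test or Mann–Whitney test directly after the paired test, followed by repeated ANOVA and covariance analysis. Order within a paragraph is not a hierarchy. A full protocol or analysis plan, not shown here, may say which test decides.

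Much of this stands. A reader might infer that the paired tests are the main efficacy analysis, or that the trial's question has no between-arm analysis. The article supports neither.

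A reader might also infer that the within-arm tests are bound to be significant with an inert capsule. That goes too far. For weight it nearly holds if the mean loss reaches about 2.5 kg at an SD of 2.85, but the chance is only 12% to 61% at 0.5 to 1.5 kg, and full adherence is a best case in patients selected for food addiction. Nor can the figures of over 99% and 25% apply to the same outcome: where p exceeds 99%, p(1−p) is under 1%.

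Finally, the objective, "the effect of probiotic supplementation with a weight-reducing diet and psychotherapy intervention", can be read as a package effect for which there is no control arm. But the Discussion states the aim as the effect of probiotic supplementation, and the placebo arm makes the contrast clear. That wording is an editorial matter.

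The reply does not remove the point. The within-arm tests are a stated choice, not something left out of a condensed article. The planned between-group t-test is valid under randomisation, but it compares end values although the primary outcomes are changes. The listed covariates omit baseline weight and baseline food addiction score, and the repeated ANOVA's time term would share the paired test's flaw. Nothing stated tells the reader which result counts.

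**Conclusion.** The point holds as a matter of interpretation and hierarchy, not as a missing analysis. Within-arm tests are planned on an equal footing with between-arm tests in a design where they cannot isolate the capsule.

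For weight, their chance of significance with an inert capsule runs from about one in three at 1 kg mean loss to near certainty at 3.3 kg. This rests on 20 per arm and on reading 2.85 as the SD of change; a larger SD lowers it. For the food addiction score the added push from regression to the mean is real but of uncertain size. For the hormones no figure can be given. The 25% false-lead rate is a ceiling, nearly reached for weight at about 1.5 kg loss.

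The text should be corrected before analysis. The design itself is not at fault.

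**What to change.** In the Statistical analysis section:

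1. Drop the paired t-test and Wilcoxon test as inferential analyses. Report mean change within each arm with a 95% CI, as description, without p-values.
2. State that conclusions about the probiotic rest on the between-arm difference at week 12, adjusted by ANCOVA for the baseline value of the same outcome. Name weight and food addiction score explicitly, since the present covariate list does not include them.

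Optionally, reword the objective as the effect of adding a probiotic, versus placebo, to diet and CBT.

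The cost is the loss of the within-arm p-values. Data collection, sample size and patient burden are unchanged.
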